### Primary feasibility outcomes

**
*Progression criteria.*
** Progression criteria into a future definitive trial will be based on the stop-go criteria assessing feasibility detailed in
Table 4 alongside consideration of adverse events and discussions with the Independent Monitoring Committee. The stop-go criteria follow a ‘traffic light’ system: Red (stop), Amber (proceed with modifications) and Green (Go). There are four categories: recruitment, intervention fidelity, intervention adherence and study retention.

**Table 4. T4:** Stop-Go Criteria.

	Red	Amber	Green
Recruitment: Number of participants recruited	< 25 participants recruited within 6 months	25–39 participants recruited within 6 months	>40 participants recruited within 6 months
Intervention fidelity: provision of the mobility and strength training	<50% undergo their individual assessment and are allocated to their group sessions	50% – 80% of participants undergo their individual assessment and are allocated to their group sessions	>80% of participants undergo their individual assessment and are allocated to their group sessions
Intervention fidelity: delivery of the mobility and strength training (fidelity assessment *via* observations based on core criteria checklist)	<50% of all key criteria are met during observed sessions	50–80% of key criteria are met during observed sessions	>80% of key criteria are met during observed sessions
Intervention fidelity: protein supplements	<50% of participants receive the protein supplements *via* home delivery as intended	50–80% of participants receive the protein supplements *via* home delivery as intended	>80% of participants receive the protein supplements *via* home delivery as intended
Intervention adherence: participant attendance at the mobility and strength training	On average, < 8/16 sessions (50%) of sessions attended by 70% or more participants	On average, 8-10/16 session (50–69%) of sessions attended by 70% or more participants	On average, at least 11/16 sessions (70%) attended by 70% or more of participants
Intervention adherence: participant adherence to the protein supplements	On average, 70% or more participants report taking protein supplements on <50% of days over 24 weeks	On average, 70% or more participants report taking protein supplements on 50–70% of days over 24 weeks	On average, 70% or more participants report taking protein supplements on ≥70% of days over 24 weeks

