Study retention: follow up rates and checking for differential loss to follow up	>30% loss to follow up at 8 months in either study arm.	29–15% loss to follow up at 8 months in either study arm.	<15% loss to follow up at 8 months in both study arms.

Recruitment: We will collect data on screening and recruitment of eligible patients from each site on a monthly basis alongside reasons for exclusion.

Intervention fidelity: Physiotherapists will record intervention provision on an intervention log, which will be monitored to assess treatment fidelity. We will also observe or record intervention sessions and assess the delivery of the interventions using a checklist of the core criteria of the intervention. We will monitor protein supplement delivery to ensure supplements are delivered to participants as intended. The central study team will also visit up to 20% of participants at home to observe home exercises and check on protein supplement intake.

Adherence with the intervention: Attendance at the exercise classes is monitored using intervention logs completed by the physiotherapists. Participants will be asked to record when they take the protein supplements in their supplement diary.

Study retention: Follow up rates will be collected, and we will evaluate if there is any differential loss to follow up by study group.

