## Trial status

The first site opened to recruitment on 01 March 2023. Recruitment is ongoing.

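### The recruitment and retention stop-go bands in Table 4 leave some results with no colour and give others two

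*Protocol article*

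**What the plan says.** The article's section on primary feasibility outcomes states: "Progression criteria into a future definitive trial will be based on the stop-go criteria assessing feasibility detailed in" Table 4. Adverse events and discussion with the Independent Monitoring Committee are to be considered as well. Red means stop, Amber means continue after changes, and Green means go.

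The two rows at issue read:

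- Recruitment. Red: "< 25 participants recruited within 6 months". Amber: "25–39 participants recruited within 6 months". Green: ">40 participants recruited within 6 months".
- Retention. Red: ">30% loss to follow up at 8 months in either study arm". Amber: "29–15% loss to follow up at 8 months in either study arm". Green: "<15% loss to follow up at 8 months in both study arms".

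The article gives no rounding rule and no rule for a result that meets two bands. The Sample size section sets a target of 50, and the randomisation section specifies 1:1 allocation, so about 25 per arm is intended.

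**The concern.** A traffic-light rule works only if every possible result has exactly one colour. These two rows fail that test in three places:

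1. A recruitment count of exactly 40 falls between Amber and Green.
2. A loss above 29% and up to 30% falls between Amber and Red.
3. Red and Amber for retention are each triggered by a single arm, so two arms with different losses can trigger both.

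The rows are listed under the primary feasibility outcomes. When a result lands on one of these points, the printed rule does not settle the colour, and someone must interpret it after the data are known. In the third case the two candidate colours are stopping and continuing with changes, which is the most consequential boundary in the table.

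**Working it through.** **Inputs.** The cut-points are from Table 4, the target of 50 from the Sample size section, and the 1:1 ratio from the randomisation section. The article states no expected loss to follow-up, so true loss is an assumption, shown from 10% to 30%, equal and independent in the two arms. No formula in the article generates the cut-points, so there is no stated figure to reproduce. The check applies the printed wording literally.

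**Recruitment.** 24 is Red; 25 and 39 are Amber; 40 has no colour; 41 is Green. 40/50 = 80% of target.

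**Retention gap.** A single arm has no band if 29% < loss ≤ 30%.

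- 20 per arm: 6/20 = 30.0%, no band.
- 24 per arm: 7/24 = 29.2%, no band unless rounded to 29%, which is Amber.
- 25 per arm: 7/25 = 28% (Amber) and 8/25 = 32% (Red), so the gap cannot be reached.

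The retention row as a whole has no colour when one arm is in the gap and the other is Green or also in the gap. At 20 per arm (40 recruits, itself the count without a recruitment colour), the probability of this is 1.2%, 3.9%, 5.7%, 5.9% and 5.0% for true loss of 10%, 15%, 20%, 25% and 30%.

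**Retention overlap.** At 25 per arm, 0–3 losses (0–12%) is Green, 4–7 (16–28%) is Amber and 8–25 (32% or more) is Red. That is 4 Amber counts and 18 Red counts. Pairs with one arm in each: 2 × 18 × 4 = 144 of 26 × 26 = 676.

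With X ~ Binomial(25, p), P(Red and Amber together) = 2 × P(X ≥ 8) × P(4 ≤ X ≤ 7):

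- p = 0.20: 2 × 0.109 × 0.657 = 0.143
- p = 0.25: 2 × 0.2735 × 0.630 = 0.345

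| Assumed true loss, both arms | Double colour, 25 per arm | Double colour, 20 per arm |
|---|---|---|
| 10% | 0.1% | 0.1% |
| 15% | 2.6% | 2.3% |
| 20% | 14.3% | 10.4% |
| 25% | 34.5% | 22.5% |
| 30% | 46.7% | 29.9% |

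**After rewording.** If the worse arm sets the colour, all 144 double-colour pairs at 25 per arm become Red, and every pair has exactly one colour.

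**The case against.** The strongest reply is that a sensible reader would resolve most of this unaided. Green needs both arms and Red needs only one, so the natural reading is that the worse arm governs; one cannot both stop and continue. On that reading the 14% and 34% are not the share of trials with an unknown result, because they would all be Red. The retention gap cannot arise at the planned 25 per arm, and 7/24 disappears if percentages are rounded to whole numbers. A count of 40 lies between two colours that both allow progression. The table is also not a mechanical switch, since safety and committee discussion are weighed too.

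Much of this stands, and it limits the severity. It does not remove the fault. The worst-arm rule and the rounding rule are inferences that the article does not state. An exact 25/25 split is not guaranteed if recruitment falls short or the blocks end unevenly. The cut-points are printed here as the rule, so the slips are not details left to a fuller document.

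A reader might go further and argue that the six-month recruitment window has no start date, so the colour could be chosen after accrual is known. The Trial status section says "The first site opened to recruitment on 01 March 2023. Recruitment is ongoing", and the article is dated April 2024, which might suggest that a window counted from the first opening was already Red. The documents do not support this. A condensed article may leave the start of the window to the full protocol. No recruitment count is given, the status line may not have been current at publication, and constant accrual would have to be assumed. Nothing shows that any colour was chosen afterwards.

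**Conclusion.** The point holds in a limited form. On the literal wording, three faults are certain: 40 recruits has no colour, loss above 29% and up to 30% has no band, and one arm above 30% with the other at 15–29% is both Red and Amber. The recruitment row has only a gap; the overlap is confined to retention.

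How often the overlap would occur depends on loss rates that the article does not give. It is negligible at 10% true loss and common at 25–30%. Those probabilities assume equal, independent loss in the two arms and no unstated tie-break.

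This is a worthwhile correction to a stated decision rule. It is not a critical fault, because the colours are weighed with adverse events and committee discussion, and because no effect estimate or safety conclusion depends on them.

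**What to change.** Reword two rows of Table 4:

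- Recruitment: Red below 25, Amber 25–39, Green at 40 or more.
- Retention, applied in order to unrounded percentages: Red if either arm exceeds 30%; otherwise Amber if either arm is 15% or more; otherwise Green, meaning both arms are below 15%. The worse arm then sets the colour, and exactly 30% is Amber.

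Date the change, and make it before the results are judged against the bands, so that it cannot look like a choice of result. The cost is a few words. No additional data are needed, because the article already plans to collect recruitment and follow-up by arm.

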### Secondary exploratory outcomes

We will collect a range of clinical outcomes at baseline and 8-month follow up to determine the viability of data collection, and to inform the sample size calculation for the future definitive RCT based on the proposed primary outcome for the trial (Short Physical Performance Battery). The clinical and participant reported outcomes are listed in
Table 2.

### Adverse events

Safety reporting will begin from the time of randomisation to 8 month follow up. All study staff have been trained to report adverse events (AEs) related to the study interventions. Given the age of participants, there are foreseeable AEs that should only be reported if they occur during or within two hours of any study interventions. These include acute infections, medical instability (
*e.g.*, worsening of heart failure), vestibular disorders or stroke and fall-related injuries. We anticipate participants may experience delayed onset muscle soreness (<72 hours) upon starting a new exercise programme, which is only reported if they are more persistent or severe than expected. We would also expect that participants taking protein supplements may experience mild gastrointestinal complaints including diarrhoea, constipation, bloating and loss of appetite. Participants are made aware of these, and they should be short lived and managed by adjusting their protein supplement dose. If symptoms are more severe and longer lasting than what is expected, then they will be reportable.

A serious adverse event (SAE) is an untoward medical occurrence that results in death; is life-threatening; requires inpatient hospitalisation or prolongation of existing hospitalisation; results in persistent or significant disability/incapacity; consists of a congenital anomaly or birth defect. We will follow reporting procedures in accordance with Good Clinical Practice (GCP) to report any SAEs that are potentially related to trial procedures.

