### Randomisation, blinding and allocation concealment

Eligible participants will be randomised to Mobility and Strength Training or Mobility and Strength Training with protein supplements using a secure (encrypted) centralised web-based randomisation service provided by the Oxford Clinical Trials Unit (OCTRU). Randomisation will be 1:1, stratified by frailty (pre-frail/frail) using variable block sizes within each strata. Following randomisation, the physiotherapy team and the central study team will be notified of allocation
*via* automated email. As we are not using a placebo supplement, it is not possible to blind the participants or physiotherapists delivering the interventions (including provision of supplements). Outcome assessors will be blinded to treatment allocation.

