### Interventions

The schedule of intervention delivery is outlined in
Table 3.

**Table 3. T3:** Intervention delivery schedule.

	Mobility and Strength Training	Training + Protein Supplements
Individual pre-class appointment		
Assessment by physiotherapist to establish current ability and exercise setting. Home exercise diary introduced.	X	x
Assessment by physiotherapist to discuss protein supplement dosing and instructions. Provided with written instructions and introduced to protein supplement diary.		x
Delivery of protein supplement arranged.		x
Weeks 1–16		
Weekly group mobility and strength exercises • Group discussion including behavioural strategies to encourage adherence with home exercises (goal setting, exercise planning and problem solving) (15 minutes) • Seated warm up (5 minutes) • Exercise circuit (20 minutes): Strengthening exercises: knee extension, hip extension and abduction, sit to stand Combined hip flexor and calf stretch Balance exercise • Walking circuit (20 minutes) One session of home exercises each week (exercise diary completed). Weights for home exercises are provided if appropriate.	x	x
Protein supplements taken daily. Complete supplement diary.		x
Protein Supplement Reviews including weight checks undertaken at weeks 2, 4, 8, 12 and 16 of the programme. Referral to dietitian if needed.		x
Weeks 17–24		
Twice weekly home exercises. Complete exercise diary.	x	x
3 follow up telephone calls to review progress with home exercises conducted by physiotherapist.	X	x
Protein supplements taken daily. Complete supplement diary.		x
3 telephone supplement reviews during the follow up telephone calls. Weight is not to be monitored.		x

**
*Mobility and Strength Training.*
** All participants will be asked to undertake twice weekly mobility and strength training supported by a physiotherapist for 24 weeks using a combination of weekly group exercise (16 weeks) and home exercises (8 weeks). Group sessions are used to provide supervision and support to participants and promote adherence to long term exercise. This is a pragmatic approach to strength and mobility training that can be implemented within NHS physiotherapy departments without the need for specialist exercise equipment. We have delivered a similar programme for participants with mobility limitations due to spinal stenosis, which was well attended, the exercises were well tolerated and enjoyed by participants
^
13,
34
^.

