^. If a participant has a BMI of 30 or more, then the recommended dose of protein is 75% of the calculated amount based on weight (as per usual clinical practice)
^
38
^. Additionally, if a participant has an eGFR between 30-60 ml/min/1.73 m
^2 ^(indicating a moderate reduction in renal function), protein intake will be limited to 1.3 g/kgBW/day. This is the maximum dose recommended for this patient group by The Kidney Disease Improving Global Outcomes (KDIGO) guidelines.

On a day when participants undertake Mobility and Strength training (at the hospital or at home), they will be advised to take one of their drinks of the supplement directly after the exercise session. Participants will complete a protein supplement diary to monitor adherence and record any side-effects experienced. Participants will be monitored and weighed at regular reviews (
Table 3). If a participant is experiencing gastro-intestinal problems, then they will be advised to reduce the dose by a half and gradually increase the dose back to the recommended amount over four days to improve tolerance. If a participant has lost >10% of their weight or is reporting ongoing intolerance issues, then participants will be reviewed by the main study team dietitian to decide if the protein supplement dose needs to be adjusted or other dietary advice given.

The chosen supplement also contains vitamin D and calcium. If participants are already taking over the counter supplements, then they will be asked to stop taking them while they are on the protein supplements. If participants are already on prescribed supplements, then the physiotherapist will liaise with the participant’s general practitioner to adjust their prescription to ensure daily maximum doses are not exceeded (Vitamin D: maximum of 4,000 IU per day; Calcium: maximum of 1 g per day).

All participants will attend the same exercise sessions. Supplement reviews will be conducted outside these sessions and participants will be asked not to discuss them in the groups. Groups will be run this way to so sites can fill the exercise groups in a timely way.

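### Read literally, the two-hour rule for foreseeable adverse events gives the supplement arm about 2.7 to 5.0 times the reporting window of the exercise-only arm

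*Protocol article*

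**What the plan says.** The Adverse events section sets a special rule for a list of events expected at this age: "there are foreseeable AEs that should only be reported if they occur during or within two hours of any study interventions". The list covers acute infections, medical instability, and "vestibular disorders or stroke and fall-related injuries". Delayed muscle soreness, gastrointestinal complaints and serious adverse events have their own rules in the same section, and none of those mentions two hours.

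The supplement counts as a study intervention. The section on randomisation and blinding refers to "physiotherapists delivering the interventions (including provision of supplements", and the section on withdrawals treats supplements and exercise as separate parts of the programme.

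Exposure differs by arm. On exercise, the Interventions section says "All participants will be asked to undertake twice weekly mobility and strength training supported by a physiotherapist for 24 weeks". Table 3 gives weeks 1–16 a weekly group session plus "One session of home exercises each week (exercise diary completed", and weeks 17–24 two home sessions a week. For the supplement arm alone, Table 3 adds "Protein supplements taken daily. Complete supplement diary" in both periods. That arm also has a further recording route: "Participants will complete a protein supplement diary to monitor adherence and record any side-effects experienced".

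Progression to a definitive trial rests on the stop-go criteria "alongside consideration of adverse events and discussions with the Independent Monitoring Committee".

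**The concern.** The window opens on any study intervention, and one arm has many more intervention occasions than the other. A fall or infection that has nothing to do with treatment is therefore more likely to land inside a window in the supplement arm. If true rates are equal, a by-arm table of the listed events would still lean against the supplement.

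Adverse events are weighed when deciding on progression. The feasibility trial also tests procedures for a definitive trial, where the same rule would act on a much larger comparison. Nothing in the article limits the rule to exercise sessions or evens it out between arms.

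**Working it through.** The protocol gives no figure for the reporting window, so there is none to reproduce. The hours follow from the schedule.

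**Inputs from the protocol**
- Exercise, both arms: 16 group + 16 home + 8 × 2 home = 48 sessions over 24 weeks.
- Group session (Table 3): 15 + 5 + 20 + 20 = 60 minutes.
- Supplement, one arm: 24 × 7 = 168 days, of which 168 − 48 = 120 have no exercise session if each session falls on its own day.
- On exercise days one drink is taken directly after the session.

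**Assumptions**
- Home sessions also last 60 minutes (length not given).
- The post-exercise drink falls wholly inside the exercise window, and other drinks open separate two-hour windows.
- One or two servings a day (k = 1 or 2). Servings are tailored, so this is a range. For an assumed 70 kg participant with a baseline of 0.99 g/kg, the 1.6 g/kg aim leaves 0.61 × 70 = 42.7 g, and 42.7 / 20.7 = 2.1 servings. Under the 1.3 g/kg limit it is 0.31 × 70 / 20.7 = 1.0.

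**Window per participant over 24 weeks**
- Exercise-only arm: 48 × (1 + 2) = 144 h.
- Supplement arm: 48 × [3 + 2(k − 1)] + 120 × 2k.
  - k = 1: 144 + 240 = 384 h; 384 / 144 = 2.7.
  - k = 2: 240 + 480 = 720 h; 720 / 144 = 5.0.

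**With 70% of servings taken and all sessions attended**
- k = 1: 144 + 0.7 × 240 = 312 h; ratio 2.2.
- k = 2: 48 × (3 + 1.4) + 0.7 × 480 = 547.2 h; ratio 3.8.

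**Sensitivity at full intake**
- With 40-minute sessions the ratios are 368 / 128 = 2.9 and 704 / 128 = 5.5.
- If two daily drinks are taken together, the ratio falls back to the one-serving value.

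**Expected counts.** Assume 25 per arm, one listed background event per person-year, and events spread evenly over time. Expected reportable events are 25 × hours / 8760:
- Exercise-only arm: 25 × 144 / 8760 = 0.4.
- Supplement arm: 25 × 384 / 8760 = 1.1 (k = 1) to 25 × 720 / 8760 = 2.1 (k = 2).

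The gap is 0.7 to 1.6 events. It scales with the assumed rate: 0.3 to 0.8 at half that rate, and 1.4 to 3.3 at twice that rate.

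**The case against.** The strongest reply is that relatedness governs. Just before the rule, the protocol says staff are trained to report events related to the study interventions. The two-hour rule may then only narrow that set, and a coincidental infection would not become reportable because a drink came shortly before it. On that reading counts need not scale with window hours. This stands as a limit on certainty. The text does not say that both conditions must be met, so the literal reading remains open, and sites could differ.

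Staff might also take study interventions to mean exercise sessions only, which would make the ratio 1. The article does not say so, and its blinding section points the other way.

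The plan summarises safety descriptively, sets no adverse event threshold in the stop-go table, and has an Independent Monitoring Committee that can look at each event. With so few events expected, this limits the harm in the present trial, and that point stands in full.

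Extra review of a product given to one arm is ordinary safety follow-up. Both arms also share the group sessions, the three calls and the 8-month visit. The supplement diary and reviews are therefore not a fault in themselves. They matter only if what they find is put into a by-arm count.

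A reader might infer that delayed supplement harm goes unseen. The documents do not support this. Gastrointestinal complaints are reportable by severity and duration, serious events by potential relatedness, and eGFR is measured in both arms at baseline and 8 months.

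**Conclusion.** The point holds as a fault in the wording of the rule, with modest consequences here. Read literally, the supplement arm's window is about 2.7 times (one serving a day) to 5.0 times (two servings) that of the exercise-only arm, or about 2.2 to 3.8 times at 70% intake. With equal background rates, by-arm counts of the listed events would tend to be higher in the supplement arm, though probably by only one or two events in 50 participants. The size rests on 60-minute sessions, non-overlapping drinks, events spread evenly over time and the assumed event rate. The direction follows from the rule and the schedule.

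A reader might infer a ratio of seven or more. That needs either three servings a day (1056 / 144 = 7.3) or leaving session time out of the window (672 / 96 = 7.0 at two servings). The rule includes time during the session. Three servings would supply 3 × 501 = 1,503 mg of calcium, in tension with the 1 g daily maximum that the Interventions section states. Two servings give 1,002 mg, about at that figure. The tailoring rule and this maximum should be reconciled, and three servings is not a sound basis for the estimate.

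Nor do the documents support saying that the rule will decide progression. Adverse events are one consideration there, without a numerical criterion.

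**What to change.** For any by-arm summary of the listed foreseeable events, count only those that occur during or within two hours of an exercise session, group or home. Both arms have the same scheduled sessions, so the planned window is 144 h in each and the ratio is 1.0.

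Report events captured only through supplement intake, the supplement diary or the supplement reviews separately and descriptively for the supplement arm. Use the ProFaNE falls and injury data, already collected in both arms at 8 months, for the between-arm description of falls. Leave relatedness-based reporting of serious events and the separate gastrointestinal rule as they are.

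The cost is a tag on each adverse event record showing which intervention opened the window, and slightly fewer events in the by-arm count.

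A wider remedy, asking both arms about the listed events at any time, is not advised. At the assumed one event per person-year it would bring in about 50 × 8/12 = 33 events, against 0.4 + 1.1 = 1.5 to 0.4 + 2.1 = 2.5 under the present window. It would undo the restriction that the protocol adopted because of participants' age.

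### Supplement gastrointestinal symptoms are reportable under an *and* rule but muscle soreness under an *or* rule; read literally, this could under-count non-serious intolerance

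*Protocol article*

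**What the plan says.** All statements are in the protocol article.

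- **General duty (Adverse events).** "All study staff have been trained to report adverse events (AEs) related to the study interventions".
- **Muscle soreness (Adverse events).** Delayed onset soreness is anticipated on starting the exercise programme, "which is only reported if they are more persistent or severe than expected".
- **Gastrointestinal symptoms (Adverse events).** The expected class is described first: "participants taking protein supplements may experience mild gastrointestinal complaints including diarrhoea, constipation, bloating and loss of appetite". Participants are told of these, and "they should be short lived and managed by adjusting their protein supplement dose". The threshold follows: "If symptoms are more severe and longer lasting than what is expected, then they will be reportable".
- **Serious events (Adverse events).** Good Clinical Practice procedures are followed "to report any SAEs that are potentially related to trial procedures".
- **Other records of side effects (Interventions, Protein supplements).** Participants note side effects in the supplement diary, and those "reporting ongoing intolerance issues" are reviewed by the study dietitian.
- **Use of the data (Primary feasibility outcomes, Progression criteria).** The stop-go table is applied "alongside consideration of adverse events and discussions with the Independent Monitoring Committee".
- **Objectives (Abstract).** Tolerance is named with fidelity and adherence in the second primary feasibility objective. Table 4 has rows for recruitment, fidelity, adherence and retention, and none for tolerance.

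**The concern.** Two reporting thresholds in one paragraph use the same two dimensions and join them in opposite ways, with no reason given. Soreness can occur in both arms, because both do the exercise programme. The gastrointestinal symptoms are the only expected effects that the Adverse events section ties to the supplement, and the supplement is the only planned difference between the arms. The narrower wording therefore falls on the component that the definitive trial would test.

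Adverse events are considered when deciding on progression, and no stop-go row measures tolerance directly. If sites apply the gastrointestinal sentence literally, the adverse event data could give an incomplete picture of how well the supplement is tolerated. If some sites apply it literally and others do not, the counts are not comparable between sites.

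**Working it through.** No power, rate or sample size calculation bears on this point. The check is a reading of the two rules over every combination of severity and duration, for non-serious symptoms.

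| Severity against expectation | Duration against expectation | Soreness rule (*or*) | Gastrointestinal rule (*and*), read literally |
|---|---|---|---|
| not exceeded | not exceeded | not reportable | not reportable |
| exceeded | not exceeded | reportable | not made reportable by this sentence |
| not exceeded | exceeded | reportable | not made reportable by this sentence |
| exceeded | exceeded | reportable | reportable |

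The rules agree in the first and last rows and differ in the two middle rows. These are patterns, not event frequencies, so the table says nothing about how many episodes fall in each row.

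The remaining question is whether another route in the article turns the middle rows into adverse event reports.

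1. **Serious event route.** It has no duration condition. A brief gastrointestinal episode that meets a seriousness criterion, such as inpatient admission, and is potentially related is reported. This removes serious cases from the second row and leaves the non-serious ones.
2. **Supplement diary.** It takes any side effect, with no severity or duration threshold. Table 2 lists it as intervention data. The article does not say that an entry produces an adverse event report.
3. **Supplement and dietitian reviews.** Table 3 schedules reviews at weeks 2, 4, 8, 12 and 16 and three by telephone in weeks 17–24. Ongoing intolerance goes to the dietitian. The third row is therefore a case the article itself foresees, but referral is not stated to produce an adverse event report either.
4. **General duty.** Staff report adverse events related to the interventions. Whether this brings back the two middle rows depends on how the gastrointestinal sentence is read, which is taken up under the objection.

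Scale: the target is 50 participants randomised 1:1, so about 50 / 2 = 25 per arm. One supplement-arm participant whose intolerance is not reported changes that arm's proportion by 1 / 25 = 4 percentage points. The article gives no expected rate of gastrointestinal symptoms and no split by pattern, so the number affected cannot be derived.

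**The case against.** The strongest reply is that the gastrointestinal sentence states when symptoms will be reportable, not that they are reportable in no other case. The soreness rule contains the word *only*; the gastrointestinal rule does not. The expected class is limited to mild, short-lived complaints. A severe episode is not mild and one lasting months is not short lived, so both arguably leave the class and return to the general duty to report related adverse events. The *and* may simply be loose prose for two ways of exceeding expectation.

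This stands as far as it goes: the text is ambiguous and not a definite exclusion. A reader might infer that severe-but-brief or mild-but-persistent intolerance is never reported. The documents do not support that, because of this argument and because serious related events are reported whatever their duration. But a threshold that needs such an argument to work as intended can be applied differently from site to site.

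A second reply is that intolerance is recorded elsewhere: in the diary, the review logs and the dietitian reviews, with supplement adherence having its own stop-go row. This also stands in part, since the information is not lost. A reader might infer that the monitoring committee will see an understated safety summary. The article does not say that adverse event forms are all the committee sees, so that is not shown. Two gaps remain. The progression text names adverse events, and none of these records is stated to feed them. The adherence row counts days on which the supplement was taken, so someone who keeps taking it despite symptoms counts as adherent.

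Third, selective reporting is the general approach here: infections, medical instability, vestibular disorders or stroke and fall-related injuries are reported only if they occur during or within two hours of an intervention. That is true, and it rules out describing exercise harms as fully reported. The valid contrast is the narrower one between the soreness and gastrointestinal rules.

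Finally, the full protocol or study manual may define these terms more closely. That could settle practice at sites, but the article states this rule explicitly and it conflicts with its neighbour, so this is not a matter of missing detail.

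**Conclusion.** The point holds as an inconsistency in a stated rule. Read literally, the gastrointestinal sentence does not make non-serious severe-but-brief or mild-but-persistent symptoms reportable, while the soreness rule covers both patterns. This could under-count supplement intolerance in the adverse event data considered for progression. It matters more than a wording slip usually would, because tolerance is a primary objective that no stop-go row measures directly.

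The size is unknown: two of the four severity-by-duration combinations are affected, and each missed participant is worth about 4 percentage points in an arm of about 25. The conclusion assumes that sites follow the sentence literally and that diary entries and dietitian referrals do not lead to adverse event reports; the article settles neither. No Table 4 threshold uses an adverse event count, so the effect on progression would be through judgement and not through a traffic-light result. The correction is worth making because it is cheap and the rule concerns the component under test.

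**What to change.** Reconcile the two sentences in the Adverse events section so that the same connective joins severity and duration in both. Replacing *and* with *or* in the gastrointestinal sentence would match the soreness rule and make both middle patterns reportable. Tell the sites of the change so that all apply one threshold.

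This concerns reporting only; dosing and the management of symptoms stay as they are. The cost is a one-word change, a note to sites and a few more adverse event forms. The supplement arm's event count may be slightly higher as a result. Because recruitment had already opened when the article was published, the report should state from what date the reconciled wording applied.
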